**Summary**

*Plasmodium falciparum* causes malaria and approximately 665 000 deaths each year. Chloroquine and sulphadoxine-pyrimethamine resistant *P. falciparum* are widespread. An artemisinin derivative combined with lumefantrine, amodiaquine or piperaquine is therefore recommended for the treatment of malaria in Africa. However, artemisinin resistance appears to be developing and resistance/tolerance to amodiaquine and lumefantrine exists.

We are presently monitoring malaria treatment in Guinea-Bissau. Preliminary data indicates that the effectiveness and availability of artemether-lumefantrine, the 1st line drug, is poor and approximately 50% of children are treated with quinine. Consequently there is a need for another treatment option. Dihydroartemisinin-piperaquine has been shown to be efficacious and well tolerated in several African countries and is therefore such an option.

We propose to conduct clinical trials comparing the safety, efficacy and effectiveness of artemether-lumefantrine and dihydroartemisinin-piperaquine.

**Background**

*Plasmodium falciparum* causes malaria and approximately 665 000 deaths each year. Previously, chloroquine and sulphadoxine-pyrimethamine were the principle drugs for the treatment of malaria. Due to widespread resistance to these drugs[1](#_ENREF_1), the World Health Organization recommends that *P. falciparum* in Africa should be treated with artemisinin + amodiaquine, artemether + lumefantrine (AL) or dihydroartemisinin + piperaquine[2](#_ENREF_2). However, resistance to artemisinins appears to be developing, resistance to amodiaquine exists[2](#_ENREF_2) and treatment with AL rapidly selects for parasites with increased tolerance (5 times higher inhibitory concentration) to lumefantrine[5-7](#_ENREF_5).

In Guinea-Bissau, chloroquine remained efficacious until replaced by AL. This is explained by the use of a unique well tolerated high dose treatment schedule [8-10](#_ENREF_8). Since the introduction of AL in 2008, the number of children with malaria has increased manyfold in Bissau in contrast with other African countries. Our data suggests that this increase is due unavailability of AL, poorer than expected effectiveness of AL and to an increased use of the second-line drug quinine. Quinine is typically given for 3 instead of 7 days and has very poor efficacy when used thus[11](#_ENREF_11). To counter this, Guinea-Bissau needs an alternative cheap and easily dosed 2nd line drug that can also be used when AL is not available or when funding for AL no longer exists.

Dihydroartemisinin+piperaquine (DP) is a safe and well tolerated artemisinin based combination[12](#_ENREF_12). DP is taken once daily and has been shown to be highly efficacious (>95%) in several African settings. DP also protects from re-infection for longer than AL[14](#_ENREF_14). As such this is a drug that could become an attractive treatment option in Guinea-Bissau. It has however, never been used in the country.

**Aim**

The overall aim is to determine the efficacy, effectiveness and safety of artemether + lumefantrine and dihydroartemisinin + piperaquine.

Specific aims are to

A) Conduct an efficacy study with artemether + lumefantrine and dihydroartemisinin + piperaquine

B) Conduct an effectiveness study with artemether + lumefantrine and dihydroartemisinin + piperaquine

**Method**

**A. Efficacy and safety of artemether + lumefantrine and dihydroartemisinin + piperaquine for the treatment of uncomplicated malaria in Guinea-Bissau**

**1. Objectives**

1. To measure the efficacy and safety of AL and DP in children aged 6 months to 12 years suffering from uncomplicated *P. falciparum* malaria.
2. To determine the capacity of each drug combination to protect against re-infection.
3. To differentiate recrudescence from re-infections using PCR based methods
4. To determine whole blood concentrations of lumefantrine and piperaquine the week before reparasitaemia
5. To determine haemoglobin values on days 0, 3 and 42
6. To determine differential white blood cell counts on days 0, 3, 7, 14 and 21
7. To determine genetic polymorphisms in *P. falciparum* causing reparasitaemia,
8. To culture parasites from 50 children for further characterisation of *P. falciparum* geno- and phenotypes.

**2. Methods**

**Study design**

This will be an open label, randomized, non inferiority trial conducted at the Bandim health centre, Guinea-Bissau. Children with uncomplicated malaria who meet study inclusion criteria will be enrolled, randomised to treatment with either AL or DP, treated on site and monitored for 42 days. The follow up will consist of a fixed schedule of check-up visits and corresponding clinical and laboratory examinations as in previous studies of ours. The proportion of children experiencing therapeutic failure during the follow-up period will be used to estimate the efficacy of the study drugs. PCR analysis will be used to distinguish between a true recrudescence due to treatment failure and episodes of re-infection.

**Study Site and population**

Children aged 6 months to 12 years with uncomplicated *P. falciparum* malaria that attend the Bandim health centre.

**Timing and duration of the study**

The study is expected to start in October 2012 and continue until 350 children are included which we believe will take approximately one year.

**Inclusion criteria**

A) Age ≥6 months, and <13 years. B) Mono-infection with *P. falciparum* detected by microscopy. C) Parasitemia of 1.000-200.000/µl asexual forms. D) Axillary temperature ≥37.5 ˚C or a history of fever within 24 hours. E) Ability to swallow oral medication.

F) Ability and willingness to comply with the study protocol for the duration of the study and to comply with the study visit schedule. G) Informed consent from a parent or guardian

**Exclusion criteria**

A) Signs or symptoms of severe malaria including the following symptoms

Prostration. Impaired consciousness. Respiratory distress. Repeated generalised convulsions (three or more per 24 hours or 2 witnessed seizures in 24 hours). Circulatory collapse. Abnormal bleeding. Jaundice. Haemoglobinuria (dark red/black urine). Severe anaemia (Haemoglobin <5g/dl). Hyperparasitaemia (>200.000/ µl asexual forms)

B) Presence of general danger signs in children under 5 including the following

Prostration. Respiratory distress. Haemoglobin <5g/dl. Two or more convulsions within 24 hours. Persistent vomiting

C) Presence of severe malnutrition. D) Any evidence of chronic disease or acute infection other than malaria. E) Regular medication which may interfere with antimalarial pharmacokinetics. F) History of hypersensitivity reactions or contraindications to AL, DP or quinine. G) Subjects with known cardiac arrhythmias or with congenital prolongation of the QTc-interval and patients who are taking medicinal products that are known to prolong the QTc interval as outlined in the summary of product characteristics for Eurartesim®. H) Domicile outside the study area.

**Loss to follow up**

If a child is not seen on the day of follow up the child will be sought at home on two consecutive days and if possible contacted by mobile phone. At each subsequent weekly follow up three new attempts to see the child will be made.

**3. Treatment**

**Antimalarial treatment**

Treatment with AL will be given according to a 6-dose regime shown below. Treatment with DP will be given according to a 3 dose regime. Tablets of AL (20 mg artemether and 120 mg lumefantrine) will be obtained from the manufacturer. Tablets of DP (Eurartesim®) with 160mg/20mg or 320mg/40mg if piperaquine/dihydroartemisinin will be obtained from Sigma-Tau**.**

Artemether-lumefantrine dosing

| **Body weight in kg**  **(age in years)** | **No. of tablets recommended**  **And approximate timing of dosing** | | | | | |
| --- | --- | --- | --- | --- | --- | --- |
| **0 h** | **8 h** | **24 h** | **36 h** | **48 h** | **60 h** |
| 5–14 (<3) | 1 | 1 | 1 | 1 | 1 | 1 |
| 15–24 (3–9) | 2 | 2 | 2 | 2 | 2 | 2 |
| 25–34 (9–14) | 3 | 3 | 3 | 3 | 3 | 3 |
| >34 (>14) | 4 | 4 | 4 | 4 | 4 | 4 |

Dihydroartemisinin-piperaquine dosing

| **Body weight in kg** | **Tablet strength PPQ/DHA**  **in mg** | **No. of tablets recommended**  **and approximate timing of dosing** | | | | | |
| --- | --- | --- | --- | --- | --- | --- | --- |
|  |  | **0 h** | **8 h** | **24 h** | **36 h** | **48 h** | **60 h** |
| 5 to <7 | 160/20 | 1/2 | 0 | 1/2 | 0 | 1/2 | 0 |
| 7 to <13 | 160/20 | 1 | 0 | 1 | 0 | 1 | 0 |
| 13 to <24 | 320/40 | 1 | 0 | 1 | 0 | 1 | 0 |
| 24 to <36 | 320/40 | 2 | 0 | 2 | 0 | 2 | 0 |
| 36 to <75 | 320/40 | 3 | 0 | 3 | 0 | 3 | 0 |

PPQ = piperaquine, DHA = dihydroartemisinin

**Block Randomization**

Identical slips of paper specifying treatment arm AL or DP will be put into an envelope. Each envelope will contain 20 slips from each group and children will randomly select one slip.

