**Follow up**

Children will be given a unique personal identification number and be given treatment after informed consent. The basic follow up schedule is shown below. Treatments, information to the children, clinical observations and adverse events will be recorded in the clinical record forms. The children will come to the health centre on days 0, 1, 2, 3, 7, 14, 21, 28, 35 and 42. If a child is not seen at the health centre he/she will be visited at home.

Table 3. Study outline

| Action | Study Day | | | | | | | | | |
| --- | --- | --- | --- | --- | --- | --- | --- | --- | --- | --- |
|  | 0 | 1 | 2 | 3 | 7 | 14 | 21 | 28 | 35 | 42 |
| Clinical Records Form 1 | + | + | + | + |  |  |  |  |  |  |
| Clinical Records Form 2 |  |  |  |  | + | + | + | + | + | + |
| Standard physical examination | + | + | + | + |  |  |  |  |  |  |
| Body weight | + |  |  |  |  |  |  |  |  |  |
| Thick and thin smear$ | + | + | + | + | + | + | + | + | + | + |
| Temperature | + | + | + | + | + | + | + | + | + | + |
| 100μL of blood on filter-paper for genotyping or drug analysis* | + |  |  |  | + | + | + | + | + | + |
| Haemoglobin level (Haemocue™) | + |  |  | + |  |  |  |  |  | + |
| Differential count (Haemocue™ WBC DIFF) | + |  |  | + | + | + | + |  |  |  |
| 200μL of blood for in vitro culturing# | + |  |  |  |  |  |  |  |  |  |

$ Twice daily on days 0, 1 and 2. *The volume of blood spotted on to filter-papers should be exactly 100μL. # from 50 children

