**7. Sample size**

The PCR corrected day 42 ACPR of AL was 97% in 2008 ( = before the national recommendation was changed in favour of A). It is likely that DP should be as efficacious as AL and it is therefore appropriate to conduct a non-inferiority trial[13](#_ENREF_13). Assuming 97% ACPR for both treatments, 5% significance level (alpha), 80% power (1-beta) and a non-inferiority limit (d) of 5% 144 children are required in each arm. Assuming a 20% loss to follow up a total of 346 children should be included.

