**Treatment**

Randomisation and treatment allocation will be as for the efficacy study. Medication will be provided but there will not be observed intake and there will be no visit to the health centre on the afternoon of day 0 or on days 1, 2 or 3. Follow up, sampling and data collection will be identical from day 7 and onwards.

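### Allocation by drawing loose, unnumbered slips in an open-label trial allows an untraceable redraw and leaves no planned sequence to check against, in both studies

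*Protocol*

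**What the plan says.** The allocation procedure is two sentences in Protocol part A, 3. Treatment, Block Randomization: "Identical slips of paper specifying treatment arm AL or DP will be put into an envelope", and "Each envelope will contain 20 slips from each group and children will randomly select one slip". An envelope is therefore a block of 40 at 1:1, and the wording implies a series of envelopes used in turn.

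Part A, 2. Methods, Study design sets the blinding: "This will be an open label, randomized, non inferiority trial". Part A, 5. Study Assessment, Follow up says: "Children will be given a unique personal identification number and be given treatment after informed consent". That section has treatments entered in the clinical record form, but it does not connect the identification number to a slip or to a position in a sequence. Part B, Treatment carries the method over: "Randomisation and treatment allocation will be as for the efficacy study".

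The protocol does not say that a drawn slip is kept out of the envelope, that the draw is witnessed or logged, who holds the envelope, or when the next one is started.

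**The concern.** Allocation concealment needs an order fixed before enrolment, hidden from the people enrolling, and recorded so that each assignment can be checked later. The slip draw supplies a random mechanism but no fixed order and no record. If the first slip is not the one hoped for, it can go back and another can be drawn. The envelope still ends with 20 of each arm used, so its contents show nothing.

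The document itself gives opportunity and expectation. Study nurses examine the children and obtain consent. Two eligibility items call for judgement: willingness to comply, and evidence of chronic disease or another acute infection. Because treatment is open, staff can see earlier allocations and may count what remains. The Summary describes the effectiveness of artemether-lumefantrine (AL) locally as poor, and part B, Sample size expects about 80% for AL against 90% for dihydroartemisinin-piperaquine (DP).

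At stake is comparability of the arms at baseline in both comparisons. Selection bias enters before treatment, and a larger sample does not remove it.

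**Working it through.** **Inputs.** Slips per arm in an envelope: m = 20 (Block Randomization). Children: 346 in study A (part A, 7. Sample size) and 474 in study B (part B, Sample size). Part A, Timing and duration gives 350 for study A. Drawing without replacement within an envelope is assumed, as the section heading implies, although the text does not say so.

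**The plan's own figure.** The allocation section states no error rate or probability. The size of study A reproduces: with 97% in both arms, margin 5%, one-sided alpha 0.05 and 80% power, n = (1.645 + 0.842)² × 2 × 0.97 × 0.03 / 0.05² ≈ 144 per arm, and 288 × 1.2 = 345.6, so 346. It is used here only to count envelopes.

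**Redraw.** Suppose one unrecorded second draw is taken whenever the first slip is not the preferred arm.
- First slip returned, full envelope: 1 − 0.5 × 0.5 = 75.0%.
- First slip held out during the second draw, full envelope: 1 − (20/40) × (19/39) = 75.6%.
- Without a redraw: 50%.

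**Prediction by tally.** Someone who sees every draw always guesses the arm with more slips left. The expected number of correct guesses per envelope is m + (2^(2m) / C(2m, m) − 1) / 2.
- m = 20: 2^40 / C(40, 20) = 7.976, so 20 + 6.976/2 = 23.49 of 40, or 58.7%.
- m = 2 (block of 4): 16/6 = 2.667, so 2 + 1.667/2 = 2.83 of 4, or 70.8%.

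An exact recursion over the draws gives the same values.

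**Certain draws.** The expected number of draws at the end of an exhausted envelope whose arm is already known is 2m/(m + 1).
- m = 20: 40/21 = 1.905 of 40, or 4.8%.
- m = 2: 4/3 = 1.33 of 4, or 33.3%.

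Only exhausted envelopes count.
- Study A: 346/40 = 8.65, so 8 are exhausted (also 8 with 350 children). 8 × 1.905 = 15.2, about 15 children.
- Study B: 474/40 = 11.85, so 11 are exhausted. 11 × 1.905 = 21.0, about 21 children.

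The last, partly used envelope adds almost nothing. In study B it stops at draw 34, and the chance that even that draw is certain is 2 × C(20, 7) / C(40, 7) = 0.8%.

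**Illustration against the margin.** Suppose, purely as an assumption, that all 15 certain-draw children in study A went to one arm and carried double the 3% failure risk. The extra failures would be 15 × 0.03 = 0.45, or 0.45/144 = 0.3 percentage points, against a margin of 5.

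**The case against.** Drawing lots without replacement is genuine randomisation. The slips are identical, and the child draws, not the nurse. A block of 40 is much harder to predict than a block of 4, and even a perfect tally leaves about 95% of draws uncertain. The protocol already places eligibility and consent before treatment. Custody of envelopes and a draw log may exist in site procedures that are not shown. All of this stands, and it makes prediction the lesser concern. It does not answer the redraw: identical slips and the child's own hand do not prevent a second draw, and unseen procedures do not alter what the protocol fixes. Allocation belongs in the protocol, so an SAP would not be expected to cure it.

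Four stronger readings are tempting, and the documents do not support them.
- **That steering occurred.** The text shows only that it would be possible.
- **That steering could never be detected.** Treatments are recorded by child, and weight, temperature, parasite counts and haemoglobin are measured on day 0, so baseline imbalance might hint at it. Slips removed or added would disturb the 20/20 count. What cannot be seen is a slip returned and redrawn, and imbalance alone would prove nothing.
- **That staff generally know the next arm.** They would know it for about 2 draws in 40, and only if one person saw every draw, which the protocol does not say.
- **That a few steered children would decide study A.** The illustration above gives 0.3 points from certain draws. Redraws could act on any child, but the documents give no frequency for them, so no bias against the margin can be calculated.

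**Conclusion.** The concern holds as a design weakness in both studies. In an open-label trial, the stated method has no pre-generated sequence, no numbering and no recorded link between draw and child. A redraw is therefore untraceable, and planned and actual allocation cannot be compared. One redraw takes the chance of a chosen arm from 50% to about 75%. Prediction is secondary and modest: 58.7% correct guesses, and about 15 children in study A and 21 in study B with a certain allocation.

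These figures assume drawing without replacement, exhausted envelopes used one after another and, for prediction, a person who counts every draw. They measure opportunity, not bias that occurred. The change is worth making because the replacement is standard and cheap.

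**What to change.** Replace the slip draw in part A, Block Randomization, so that part B, Treatment inherits the change:
- A person who does not enrol generates the list by computer. Blocks may vary in size but should not be small, since a block of 4 raises correct guesses to 70.8%.
- Hold the assignments in sequentially numbered, opaque, sealed envelopes, one per child.
- Open the next envelope only after consent and eligibility are written on the record form.
- Enter the envelope number on the record form and in an allocation log, next to the child's identification number.

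The cost is preparing about 820 envelopes (346 + 474) and keeping a log. No extra staff or visits are needed, and the sample size is unchanged.

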**Concomitant treatment and medication that should not be used**

Paracetamol will be used to treat fever. Iron and vitamin supplementation will be given if required. Prior treatment with an antimalarial drug will not be considered as exclusion criteria. Children taking any drug with antimalarial activity (including antibiotics such as tetracycline or azithromycin) during the study period will be withdrawn.

**Rescue treatment**

If children vomit twice, they will receive therapy with quinine intramuscularly and will be withdrawn from the study. Any child with signs of severe or complicated malaria will be treated according to recommendations of the attending nurse. If a child meets criteria for early treatment failure, he or she will receive parenteral quinine. If a child meets criteria for late treatment failure he or she will be re-treated with AL.

**4. Evaluation Criteria**

**Efficacy and safety evaluation**

Treatment outcomes will be early treatment failure, late clinical failure, late parasitological failure or adequate clinical and parasitological response as defined by the WHO[2](#_ENREF_2).

**Safety end points**

The incidence of any adverse event including neutropenia will be documented. All children will be asked routinely about previous symptoms and about symptoms that have emerged since the previous follow up visit. When clinically indicated, children will be evaluated and treated appropriately. All adverse events will be recorded in the case record forms.

Inclusion to the study will end if more than 40% of children in either study arm have reparasitaemias by day 14. This will be assessed in an interim analyses when 150 children have been included. If neutropenia (<1000 neutrofils per µl) is detected in more than 15 (10%) children the study will be stopped.

**Clinical evaluation**

All children will be evaluated by an attending study nurse and the examination will include a physical examination, body weight, body (axillary) temperature as shown in table 3

**Microscopic examination**

Two thick and thin blood films for parasite counts and species identification will be obtained as shown in table 3 and whenever a child returns to the Bandim health centre. Slides will be stained using freshly prepared Giemsa and examined with 1000 x magnification. The number of asexual parasites per 200 white blood cells will be counted or, if parasitaemia is high, the number of white blood cells per 500 parasites will be counted. Parasite density will be assessed independently by 2 qualified microscopists. Discordant results will be read a third time.

**Genotyping, antimalarial drug concentration, haemoglobin and white blood cell count**

100µL of blood will be collected on Whatman 3MM filter-paper using a capillary tube on day 0, 7, 14, 21, 28, 35, 42 and whenever reparasitaemia is detected. Filter-papers will be dried and then placed inside separate sealed plastic bags. Filter-papers and bags will be labelled with study number date and follow up day. The samples will be stored at -20˚C. Blood samples will be obtained at the same time that blood is taken for microscopy.

In order to differentiate recrudescence from a re-infection genotyping using sequential analysis of *pfglurp*, *pfmsp1* and *pfmsp2* will be done[15](#_ENREF_15).

The proportion of resistance associated genotypes in resistance associated genes including *pfcrt, pfmdr1, pfmrp1* and *pfcmu* will be determined. Genotyping will be done at Karolinska Institutet, Stockholm, Sweden and/or Universidade do Minho, Portugal.

Drug concentrations will be assessed on the week prior to reparasitaemia at Mahidol University Bangkok using high performance liquid chromatography (HPLC).

Haemoglobin concentration will be determined on day 0, 3 and 42 using a haemocueTM

At the same time that blood sampling for microscopy is done on Day 0, exactly200μL of blood will also be taken for invitro culturing from 50 patients. The blood will be put into medium and grown in vitro in an incubator at 37 ˚C. When a culture is established it will be frozen in liquid nitrogen for transport to Sweden or Portugal where extensive drug assays will be carried out.

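### The prior-week assay rule points to the enrolment sample when parasitaemia is found by day 7, and later levels lack a fixed day or a reference group

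*Protocol*

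**What the plan says.** Objective 4 of study A (Protocol, part A, 1. Objectives) is: "To determine whole blood concentrations of lumefantrine and piperaquine the week before reparasitaemia". The laboratory section (Genotyping, antimalarial drug concentration, haemoglobin and white blood cell count) turns this into an assay rule: "Drug concentrations will be assessed on the week prior to reparasitaemia at Mahidol University Bangkok".

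The same section schedules filter papers "on day 0, 7, 14, 21, 28, 35, 42 and whenever reparasitaemia is detected". Table 3 (5. Study Assessment, Follow up) describes them as "100μL of blood on filter-paper for genotyping or drug analysis" and leaves days 1, 2 and 3 blank. Collection is not restricted to children who fail, and the papers are kept: "The samples will be stored at -20˚C".

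Study B takes over objective 4, since its own Objectives section drops only day 3 haemoglobin and neutropenia. Its sampling is the same from day 7. Its Treatment section adds: "Medication will be provided but there will not be observed intake".

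**The concern.** A rule defined by the week before detection needs a usable sample in that week. For parasitaemia found at the day 7 visit there is none after enrolment, so the rule returns a paper that says nothing useful about the course the child was given.

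For later recurrences the rule works, but the sampled day moves with the day of detection and no level from parasite-free children is planned. A level from day 7 and one from day 35 reflect very different elapsed times, and nothing shows what a child who stayed clear had on the same day.

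What is at stake is how far a secondary objective can be interpreted. It matters most in study B, where intake is unobserved, there is no visit on days 1 to 3, and the protocol states no adherence measure. There the day 7 paper is the first scheduled objective evidence that tablets were taken. The rule uses it only for recurrences found after day 7 and up to day 14. The primary outcomes, sample sizes and safety rules are unaffected.

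**Working it through.** The protocol gives no figure to reproduce here, so the check sets the assay rule against the sampling calendar.

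**1. Which paper the rule selects.** Scheduled paper days are 0, 7, 14, 21, 28, 35 and 42. For each weekly visit, take the last scheduled paper before it:

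| Parasitaemia found on day | Prior-week paper | Usable as a post-treatment level? |
| --- | --- | --- |
| 7 (or earlier) | 0 | No |
| 14 | 7 | Yes |
| 21 | 14 | Yes |
| 28 | 21 | Yes |
| 35 | 28 | Yes |
| 42 | 35 | Yes |

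The rule works at five of the six weekly visits. The sampled day ranges from 7 to 35, a spread of 35 − 7 = 28 days.

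**2. Is the day 0 paper taken before dosing?** The protocol does not say so directly. It does say: "Blood samples will be obtained at the same time that blood is taken for microscopy". Microscopy confirms eligibility, and treatment follows consent (Inclusion criteria; Screening and enrolment; Follow up), so the enrolment blood should come first. One loose end is that smears in study A are made "Twice daily on days 0, 1 and 2", so a later day 0 paper is conceivable. Even that would precede most of a course whose last dose is at 48 h (DP) or 60 h (AL) in the dosing tables. In study B there is no afternoon visit on day 0, which closes that route.

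**3. Could the day 0 paper mislead?** Earlier antimalarial treatment is not an exclusion (Concomitant treatment and medication that should not be used), and the Summary names AL as the first-line drug. A day 0 paper could therefore show lumefantrine from a previous course.

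**4. What extra assays the fix needs.**
- Detection on day 7: the day 7 paper takes the place of the day 0 paper, so no net increase if day 0 is then not assayed.
- Detection on day 14: the prior-week paper already is the day 7 paper, so no increase.
- Detection on days 21 to 42: one extra assay per child.

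The increase is thus at most about one assay per case.

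**5. Rough scale, as context only.** At the planning rates, study A expects 0.03 × 144 = 4.3 PCR-corrected failures per arm. Study B expects 0.20 × 197 = 39.4 and 0.10 × 197 = 19.7 failures, together about 59. These do not count all reparasitaemia. Objective 4 also covers re-infections, and study B does not say whether its effectiveness figures are PCR-corrected. Neither set says how many children are positive by day 7.

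**The case against.** The strongest reply is that objective 4 is purely descriptive. It promises a level before reparasitaemia and nothing more. A level shortly before parasites appear can be read beside the genotypes of objective 7 as the residual drug present when they emerged, and that use needs neither a fixed day nor controls. On this view the moving sample day follows from the objective. The arms also carry different partner drugs, so levels are not directly comparable between arms whatever the day. And because papers from all children are stored, further assays could be specified in an analysis or laboratory plan that is not shown.

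Most of this stands. A reader might infer that objective 4 fails, or that the study cannot link exposure to treatment failure. The protocol supports neither reading: it states no such aim, the rule delivers for days 14 to 42, and the stored papers keep a later comparison possible. The absence of a control comparison is not an error.

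The reply does not cover parasitaemia found by day 7. The protocol itself fixes which sample is assayed, and for these children that rule selects the wrong paper. Storage makes the repair possible but does not make it part of the plan.

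A formal case-control comparison would also add little in study A. With about four confirmed failures per arm, even four of four matched pairs in one direction gives a two-sided sign test p of 2 × 0.5⁴ = 0.125.

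**Conclusion.** The point holds in a limited form. For parasitaemia found on or before day 7, the stated rule selects the enrolment paper and gives no useful level of the study drug. This affects one of the six weekly visits, in both studies. For the other five, objective 4 is met as worded, but the levels come from days 7 to 35 with no reference from parasite-free children, so they are hard to judge as low or adequate.

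The conclusion assumes that the day 0 paper is taken before the first dose, or early enough in the course to be uninformative. That is a sound inference, not stated text. The number of children affected is unknown. This is a worthwhile, inexpensive improvement to a secondary objective, most useful in study B.

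**What to change.** In the laboratory section of part A, with a matching clause in objective 4:

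- Assay the stored day 7 filter paper for every child with reparasitaemia, including those positive on day 7, in addition to the prior-week paper.
- State that the day 0 paper is not used as an on-treatment level.
- State how parasitaemia found before day 7 is handled. The paper taken at detection may be the only post-enrolment sample in those children.
- Apply the same rule in study B.

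Optionally, assay same-day stored papers from some parasite-free children in the same arm, as a descriptive reference only.

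The cost is about one extra HPLC assay on a stored paper per case, and more if reference children are added. No new visit or blood draw is needed.
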